### Statistical analysis

A Consolidated Standards of Reporting Trials (CONSORT) diagram (Fig. 1) shows the flow of participants through the trial. Baseline data including demographic variables will be summarized descriptively by trial arm but no formal statistical comparisons will be undertaken. Continuous measures will be reported as means and standard deviations while categorical data will be reported as counts and percentages.

The main analysis will use log-binomial regression for the primary outcome to estimate any difference in risks between the two arms of the study adjusting for baseline data. We will also investigate any potential clustering at the centre level and family/friends’ level and adjust for it in the regression model. A similar approach will be used for the binary secondary outcomes, namely point abstinence at weeks 5, 12 and 25, lapse between weeks 5 and 12, weeks 12 and 25 and weeks 5 and 25. A subgroup analysis of point and continuous abstinence will compare participants with or without concomitant smoking; this analysis will be conducted by exploring whether there is an interaction between the treatment arm and whether someone exclusively smokes a waterpipe or combines it with other forms of tobacco consumption.

The MPSS items will be analyzed individually, summated to give an overall score and scored in three blocks as suggested by West et al. [17]. Similar approaches will be used for the LWDS-11 [7] and SUTS [19] scales. Appropriate regression analysis will be used for each outcome, linear for the summated scores if the assumptions are met, otherwise appropriate measures will be taken, and ordered logistic regression used for the Likert-scale individual items. Analysis of AEs and SAEs will explore whether these differ by treatment arm using chi-square tests. In case of missing data, multiple imputations and appropriate sensitivity analyses will be conducted. As it is likely that more than one variable will have missing data we will use multiple imputations using chained equations (MICE). A minimum of 10 imputations will be performed; however, the final number of imputations will depend on the missing data. We will report the decisions that we make with regard to the number of imputations and the variables we use in the imputations. We will also conduct a sensitivity analysis to explore the implications of the missing-at-random assumption [20, 21]. A significance level of 0.05 will be used for the primary analysis whereas this will be 0.1 for the secondary analyses.

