**Methods/design:**

This is a two-arm, double-blind, placebo-controlled randomized trial conducted in four districts in Punjab, Pakistan. Study participants include adults using a waterpipe (with or without concomitant cigarette, bidi or other forms of tobacco smoking) on a daily basis for at least 6 months and who are willing to quit. We will individually randomize 510 participants to one of the two arms of the trial. Participants in the intervention arm will receive varenicline and behavioral support and those in the control arm will receive placebo and behavioral support. The primary outcome will be continuous abstinence for at least 6 months (week 25) which is biochemically verified by a carbon monoxide level of <10 ppm. Secondary outcomes will include biochemically verified 7-day point abstinence at 5, 12 and 25 weeks and any lapses and relapses between the different assessment points. Tertiary outcomes will include assessment of withdrawal symptoms using the Mood and Physical Symptoms Scale (MPSS), smoking dependency using the Lebanon Waterpipe Dependency Scale (LWDS-11) and monitoring adverse outcomes.

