### Sample size

The primary outcome of the study is continuous abstinence for at least 6 months between week 5 and week 25. Our previous data from a clustered randomized trial in 33 centers in Pakistan [13] with 1955 participants gave an estimate of 37% continuous abstinence at 25 weeks for the behavioral support arm of the trial. A difference of an additional 13 percentage points in the varenicline group is the minimum clinically important difference that we are interested in detecting; this is the median difference reported by the trials which looked at the effectiveness of varenicline and were included in the systematic review by Cahill et al. [8]. In order to detect an absolute difference of 13% in the varenicline plus behavioral support versus the placebo plus behavioral support group, with 80% power and 5% significance, 228 patients would be required per arm. Allowing for a 10% dropout, a total of 508 patients will, therefore, need to be recruited into the study.

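### The between-arm safety analysis is fixed as chi-square tests alone, which give no size of excess harm and no limit on it, and which are weak if serious events are uncommon

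*Protocol article*

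**What the plan says.** Adverse outcomes stand last in the abstract's list of tertiary outcomes: "smoking dependency using the Lebanon Waterpipe Dependency Scale (LWDS-11) and monitoring adverse outcomes". Their between-arm analysis is one sentence in the Statistical analysis section: "Analysis of AEs and SAEs will explore whether these differ by treatment arm using chi-square tests". No risk difference, risk ratio or confidence interval is named there. The Adverse events section covers recording, coding, causality, severity, expectedness and reporting, and adds no other comparison between arms.

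For the primary outcome the same Statistical analysis section names log-binomial regression, with the purpose of estimating a difference in risks. It extends a similar approach to the binary secondary outcomes.

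The sample size rests on abstinence alone: "with 80% power and 5% significance, 228 patients would be required per arm". No expected adverse event rate and no power or precision for safety is given. On test levels the plan says "A significance level of 0.05 will be used for the primary analysis whereas this will be 0.1 for the secondary analyses", and does not say which level applies to adverse events.

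**The concern.** The useful safety result in a placebo-controlled trial is an estimate: how many more participants had an event on varenicline, and how large an excess the data cannot exclude. A chi-square p-value answers neither question. For uncommon events in a trial sized on abstinence, a non-significant result is likely whether or not a real excess exists, so it says little by itself. A significant result for a common event would also leave the size of the harm unstated.

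The article presents this as the first randomized trial of a pharmacological agent for stopping waterpipe smoking, so later readers will want to use its safety data. The chosen method discards the part of the information they would need. It also works least well for SAEs, where small counts strain the chi-square approximation.

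**Working it through.** **Inputs from the article**
- Total sample: "We will individually randomize 510 participants to one of the two arms of the trial", taken as 510/2 = 255 per arm. Equal allocation is implied by the equal numbers per arm in the Sample size section.
- Control abstinence: 37% ("gave an estimate of 37% continuous abstinence at 25 weeks for the behavioral support arm of the trial").
- Effect: 13 points ("A difference of an additional 13 percentage points in the varenicline group is the minimum clinically important difference"), so 37% versus 50%.
- Test levels: 0.05 and 0.1, taken as two-sided.

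**Assumed, because the article gives no figure:** the control-arm event rate. A range is shown.

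**Step 1. Reproduce the plan's own sample size.** Pooled formula without continuity correction:

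n = [z(0.975)·√(2·p̄·q̄) + z(0.80)·√(p1q1 + p2q2)]² / d²

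With p̄ = 0.435 and d = 0.13:
- 1.960·√0.49155 = 1.374
- 0.8416·√0.4831 = 0.585
- n = (1.374 + 0.585)² / 0.0169 = 227.1, rounded up to 228

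For dropout, 228/0.9 = 253.3, so 254 per arm and 508 in total. This matches "Allowing for a 10% dropout, a total of 508 patients will, therefore, need to be recruited into the study". The sizing is correct for abstinence, and safety does not enter it.

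**Step 2. Power of the stated test for a doubled risk.** Normal approximation:

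power = Φ{[√n·d − z·√(2·p̄·q̄)] / √(p1q1 + p2q2)}

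Example, 2% versus 4% with n = 255 at two-sided 0.05:
- √255 × 0.02 = 0.3194
- 1.960 × √0.0582 = 0.4728
- (0.3194 − 0.4728) / √0.058 = −0.637, so power is 26%

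Full enumeration of two independent binomials (255 each, uncorrected Pearson test) agrees within about 2 points. The exact values are:

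| Control vs varenicline (assumed) | Power / missed at 0.05 | Power / missed at 0.10 |
|---|---|---|
| 1% vs 2% | 14% / 86% | 24% / 76% |
| 2% vs 4% | 26% / 74% | 37% / 63% |
| 3% vs 6% | 37% / 63% | 50% / 50% |
| 4% vs 8% | 48% / 52% | 61% / 39% |
| 5% vs 10% | 58% / 42% | 70% / 30% |
| 8% vs 16% | 80% / 20% | 88% / 12% |
| 10% vs 20% | 89% / 11% | 94% / 6% |

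By the normal approximation, power for a doubling passes 50% at a control rate of about 4.3% (level 0.05) or about 3.1% (level 0.10).

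Two variations lower the exact power at 0.05 for control rates of 1%, 2% and 3%. With 228 per arm it is 13%, 24% and 34%. With Yates correction at 255 per arm it is 7%, 18% and 30%.

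**Step 3. What an interval adds.** Illustrative counts: 5 SAE participants on placebo and 10 on varenicline, out of 255 each.
- Chi-square: p̄ = 15/510 = 0.0294. (5/255)² / (0.0294 × 0.9706 × 2/255) = 1.72, so p = 0.19.
- Risk difference: 10/255 − 5/255 = +2.0 points. Wilson limits are 2.14% to 7.07% for varenicline and 0.84% to 4.51% for placebo. Newcombe lower limit: 1.96 − √[(3.92 − 2.14)² + (4.51 − 1.96)²] = −1.1. Upper limit: 1.96 + √[(7.07 − 3.92)² + (1.96 − 0.84)²] = +5.3.
- Risk ratio: 2.0. Log standard error √(1/5 + 1/10 − 2/255) = 0.54, so the 95% interval is 0.69 to 5.8.

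The p-value alone reports no significant difference. The interval shows that an excess of about 5 points is still compatible with the data.

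**Step 4. Sparse counts.** With equal arms and T participants with an SAE in total, the expected count per arm is T/2. It falls below 5 when T is under 10, and there the chi-square approximation is weak.

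**The case against.** The strongest reply is that this is detail for an analysis plan. The article is condensed, a chi-square test is valid for comparing proportions, and nothing in the text rules out effect estimates elsewhere. It is true that their absence here does not show they are unplanned. What stands is narrower: the article does choose a safety method, and beside the estimation it specifies for the binary efficacy outcomes, it chose a bare test.

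Three stronger readings are tempting, and the article supports none of them.
- A reader might infer that a non-significant test will be reported as no safety difference. The article says only that the analysis will explore differences. It sets no such rule and states no safety conclusion.
- A reader might infer that a doubling of serious events would usually be missed. That depends on a rate the article never gives, and it reverses above about 4.3% (level 0.05) or 3.1% (level 0.10). The sentence also covers common AEs, for which power is good.
- A reader might call the lack of a safety margin a defect. No claim of equivalence or non-inferiority on safety is made, so none is required.

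It can also be said that wide intervals for SAEs are no more informative than a non-significant test, and that readers could compute intervals from reported counts. An interval does not add power. It does show the lack of information openly, where a p-value hides it, and readers should not have to supply the analysis.

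**Conclusion.** The point holds, at minor severity. The stated safety method gives no effect size and no bound on excess harm, and no other between-arm safety analysis is named. With 255 per arm, two-sided 0.05 and an assumed control SAE rate of 1% to 3%, a doubling is missed about 63% to 86% of the time; at 0.10 the range is about 50% to 76%. These figures are conditional on that assumed rate and on equal arms. Even where power is good, the test alone would not tell readers how large the harm is.

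**What to change.** Replace the sentence on AEs and SAEs in the Statistical analysis section with wording such as:

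> For any AE and for any SAE, the number and percentage of participants with at least one event will be given by arm, with the risk difference (varenicline minus placebo) and its 95% confidence interval by a score-type method (Newcombe or Miettinen-Nurminen). Safety will be interpreted from the interval. Any p-value is supplementary, with an exact test where counts are sparse. Intervals by MedDRA category are descriptive.

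The cost is a change of wording and a few lines of code, with no new data or participants. The downside is that intervals for SAEs will be wide, so the safety statement will be less reassuring.

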## Discussion

The trial will be conducted to protect the human rights and dignity of the participant as reflected in the 1996 version of the Helsinki Declaration. Participants will not receive any financial inducement to participate in the trial. In order to protect the trial participants, the following provisions will be made/upheld: the trial has been designed to minimize the burden on participants and any foreseeable risk in relation to the intervention involved; the explicit wishes of the participant will be respected including the right to withdraw from the trial at any time; the interest of the participant will prevail over those of science and society; provision will be made for indemnity by the investigator and sponsor. We will deal with key ethical issues in our research as follows:We will obtain written consent from all those who are eligible and, after having received trial information (in the local language) and sufficient time (24 h) to consider, are willing to participate. Those unable to sign will be requested to provide a thumb impression on the consent from, a common and acceptable alternative to a signature in PakistanIn line with the Data Protection Act and the Research Governance Framework, all data collected will be confidential, being identified with the unique enrollment number only assigned at the beginning of the trial. The research team will maintain the key linking these numbers with the participants’ contact details. Access to the master key register will be limited to researchers via a password-protected databaseAll investigators and collaborators at each research site will be required to submit an individual statement declaring any conflicts of interest on a yearly basis reviewed by the Independent Trial Steering CommitteeAccess to the participants’ personal details will be restricted to the necessary members of the research team only. Monitors and auditors may also need to access the data. At the end of the trial, data will be securely archived by the University of York for a minimum of 5 years

We have identified following risks associated with this application and strategies to mitigate these:Barriers to obtaining favorable opinion from the Ethics Committee: this is unlikely as this study does not pose major risks nor put undue burden on participantsDelays in obtaining approval from the Ministry of Health in Punjab, Pakistan: we have the support of tobacco leadership in Punjab for this projectLack of collaboration between investigators and hospitals: we have secured expression of interest from all four hospitals to minimize this riskStaffing recruitment and retention issues: we will ensure that all recruitment paperwork is prepared and posts are advertised in advanceRisks associated (accidents and violence) with traveling in Pakistan including: Foreign and Commonwealth Office’s (FCO) advice will be followed while making travel arrangements; we will carry out a full risk assessment according to the institutional policy before any travelSlow recruitment: our eligibility criteria are fairly broad and recruitment targets realistic based on the existing service workload and our experience in recruiting trial participants; we recruited approximately 2000 participants in a previous smoking-cessation trial in PakistanLoss to follow-up higher than expected: in the previous trial in Pakistan we found less than 10% attrition rateProtocol violations: this will be minimized through pilot work, training, supervision, monitoring and quality controlSerious adverse events (SAEs): a policy on managing SAEs will be developed as part of the protocolErrors or inconsistencies in data entry and collation: data management systems and procedures will be standardized and relevant training will be provided; quality controls will be put in place to minimize errors

Being the first RCT of a pharmacological agent for cessation of waterpipe tobacco smoking, the potential impact of this trial is likely to be high as it addresses a key public health concern. To disseminate study findings to the relevant audience, the study results will be published in leading peer-reviewed journals and presented in international public health/tobacco control conferences. The abstract will be published on the University of York official website and learning from the project will be incorporated into health promotion lectures for Master’s students of public health. The National Tobacco Control Cell will be involved at all stages of the project. A project report and a policy brief of the research process and results will be compiled. Events like No Tobacco Day will be utilized to publicize our work through leaflets, policy briefs and community talks.

## Abbreviations

AE: Adverse event
CO: Carbon monoxide
CONSORT: Consolidated Standards of Reporting Trials
FCO: Foreign and Commonwealth Office
LWDS: Lebanon Waterpipe Dependency Scale
MedDRA: Medical Dictionary for Regulatory Activities
MPSS: Mood and Physical Symptoms Scale
SAE: Serious adverse event
SSARD: Serious suspected adverse drug reaction
SUTS: Strength of Urges to Smoke
